Appendix 1 – An information sheet for children unaware of their diagnosis has been added  
The role of the Research Ethics committee has been modified in the parents/carers, young adult, and young people information sheets to state that their task is to check the study and make sure as far as possible; no harm comes to anyone from being part of the study.

Appendix 2 – Sample Consent Forms: Statement regarding use of anonymised blood samples in consent forms for parent/carers and young adults has been amended to state that they will only be used for ethically approved studies. Assent form for children unaware of diagnosis added

Appendix 5 – Acceptability questionnaire for carers – Weekends off group – Restarting continuous ART or at end of study: Question 5 reworded into two parts (a and b) to ask about the difference for the child before and after the weekend. Question 6 reworded into two parts (a and b) to ask about the difference for the carer before and after the weekend.

Acceptability questionnaire for young people – Weekends off group – Restarting continuous ART or at the end of study: Additional question introduced at beginning to ask who gives the young person their medicines (for consistency with the other questionnaires). Question 3 reworded into two parts (a and b) to ask about the difference for the young person before and after the weekend. Additional question introduced after this (now Q4) to ask about difference before and after the study.

Appendix 12 - Qualitative Substudy – Patient Information Sheets - Wording regarding timing of interviews modified; first interview to take place in early stages of the trial and second to take place towards the end of the trial. Clarification that a third interview may be conducted if feasible and that travel expenses to attend interviews will be reimbursed.

A witness signature section has been added to all the consent forms relating to this substudy in the case that the participant/carers is unable to sign and uses a thumbprint.

### **Minor changes:**

Minor re-wording for clarification: general information; 1.6; 1.7.3; 5.1; 6.1.1; 6.2; Appendix 11  
Updates to contact details: general information; Appendix 16

### **Changes to protocol version 1.3 creating version 1.4 21st January 2010**

#### **Major changes:**

[name], Chair of BREATHER Steering Committee added to authorisation of protocol.  
Compliance and funder details changed

Section 1.2, 1.5, 1.8, 1.9 -1.12, 4.1, 4.2, 7.1, 7.2, 7.6 PIS: Addition of viral load measurements and blood stores at weeks 1, 2, 3 and 8 for participants randomised to continuous ART in the pilot phase

Section 1.9-1.12, 8.5: Reduction of timepoints for cell storage

Section 4.2, 11.6: clarification of main trial primary outcome measures for participants enrolled in the pilot phase

Minor changes and corrections:

General information: Reference to EuroCoord added  
Flowsheet 1.10: Flowsheet for CT Participants in the Pilot phase added  
Appendix 2: Minor re-wording of the consent forms  
Appendix 16: IDMC membership added

### **Changes to protocol version 1.1 creating version 1.3 8th December 2010.**

Note: This protocol is named version 1.3 8th December 2010 to avoid confusion with protocol version 1.2 dated 12th August 2010 which was submitted to the Thai Research Ethics Committee in error.

Major changes:

General information: committee membership and medical experts moved to Appendix 16  
Section 1.9, 1.10, 1.11: Tanner stage examination moved from screening to randomisation visit.  
Calcium and phosphate now only at baseline and annually thereafter. Biochemistry to be carried out as per local practice.  
Section 3.2, Uganda and Romania added to list of participating countries.  
Section 5.2 : additions to exclusion criteria: creatinine, AST or ALT of grade 3 or above at screening; NVP or boosted PI regimen.  
Section 5.3, specified that siblings can be allocated into the same arm.  
Section 7.3, clarification that participants in pilot can change days off from Saturday/Sunday to Friday/Saturday, after the pilot if they wish; removal of specification that morning ART must be not be taken.  
Section 8.2, collection of ethnic origin justified and reference [39] added.  
Section 8.7: clarification of use of diary to provide information on adherence.  
Appendix 1: Deletion of reference to text-back; clarification of where information is country/substudy specific.  
Appendix 2: Addition of consent to receiving text messages, where possible.  
Appendix 4 and 5. Adherence and Acceptability questionnaires revised.  
Appendix 7. An alternative design for the participant diary added.  
Appendix 9. Toxicity grading tables updated with August 2009 revision.

Contacts and references updated.

Minor changes made for clarification; Page 1, Sections 1.2, 1.3, 1.5, 1.9, 1.10, 1.11, 2.2.1, 2.4, 5.1, 5.2, 6.2.1, 7.1, 8, 8.2, 8.4, 8.5, 8.7, 8.8, 8.10.1, 10.4, 11.4, Appendices 14 and 15.

### **Changes to protocol version 1.0 creating version 1.1 12th April 2010:**

Major changes:

- 1) Viral load cut off of 10,000 taken out of section 1.8, 7.2 and patient information sheets.
- 2) For pilot phase, option of fri/sat off ART and the attending phlebotomy visit on a Tuesday has been taken out so that the viral load is taken before recommencing ART (i.e Sat/sun off ART, viral load taken on Monday before ART recommences).
- 3) Clarification of how the young people in the pilot phase will be handled in terms of the primary outcome.
- 4) Week 1 phlebotomy visit in main trial taken out (flowsheet 1.10 amended)
- 5) Centralised viral loads to be measured at end of trial (section 8.5 and appendix 11).
- 6) Change of lipodystrophy assessment from screening visits to week 0 (flowsheets 1.9-1.11, section 8.2).

Changes to structure and minor changes to text:

- 7) Text about pilot phase and main trial specific requirements taken out of sections, 1.8, 4.2, 4.3, 6.2.2 and 6.2.3 and added to sections 1.2, 1.4, 1.5, 4.1, 4.2 and section 7 (7.1-7.5).
- 8) Thailand HIV-NAT to take part in adherence MEMS cap sub study (section 1.7.3).
- 9) Changes to wording of inclusion criteria (items 3 and 4).
- 10) Procedures for assessing efficacy text moved from section 8.9 to 4.3.
- 11) Clarification in text to sections 8.7. and 8.8 to state that both caregivers and participants should complete questionnaires, where applicable.
- 12) Clarification that week 8 visit is for the pilot phase SCT arm only, sections 1.5 and 8.5 have been amended).
- 13) Abbreviations and Glossary updated.
- 14) Contacts updated.

## APPENDIX 3: SAMPLE GP LETTER

### GP Letter

(To be printed on local headed paper)

Date:

**BREATHER:** Short-Cycle Therapy (SCT) (5 days on / 2 days off) in young people with chronic HIV-infection.

ISRCTN 97755073

Dear Dr \_\_\_\_\_

The parents of ..... (and ..... herself/himself) have agreed to participate in the BREATHER study. This is a multicentre, randomised clinical trial by the PENTA network (Paediatric European Network for the Treatment of AIDS).

The overall aim of the BREATHER trial is to evaluate the role of Short-Cycle Therapy (SCT) in the management of HIV-infected young people who have responded well to antiretroviral therapy.

The specific aim of the study is to determine whether young people with chronic HIV infection undergoing Short-Cycle Therapy of five days on and two days off maintain the same level of viral load suppression as those on continuous therapy. Acceptability, quality of life and adherence to randomised strategy will be compared.

The study will enrol at least 160 children and young people from the PENTA centres.

This young person has been allocated to receive

- ☐ continuous therapy
- ☐ SCT (5 days on/2 days off)

I enclose a summary of the trial and a patient information sheet. You will be kept up to date with your patient's progress but if you have any concerns or questions regarding this study please contact the responsible doctor:

Dr \_\_\_\_\_ at \_\_\_\_\_ (Hospital)

Tel: \_\_\_\_\_

Kind regards,

Name  
Position

Enc. Trial Summary  
Patient Information Sheets

## **APPENDIX 4: ADHERENCE QUESTIONNAIRES**

### Screening

- Adherence questionnaire for young people in both groups at screening
- Adherence questionnaire for carers in both groups at screening

### Follow-up

- Adherence questionnaire for young people in the SCT group (weekends-off) at follow-up
- Adherence questionnaire for carers in the SCT group (weekends-off) at follow-up
- Adherence questionnaire for young people in the CT group (continuous) at follow-up
- Adherence questionnaire for carers in the CT group (continuous) at follow-up

Young People  
Both Groups  
Screening

[figure not shown]

**ADHERENCE QUESTIONNAIRE FOR YOUNG PEOPLE**  
**Both Groups – SCREENING**

|                                                               |                                 |                                        |
|---------------------------------------------------------------|---------------------------------|----------------------------------------|
| Trial number: _____                                           |                                 | Date of birth:     /     /             |
| Male  Female  | Date of assessment:     /     / | Date of last clinic visit:     /     / |

*We know that it can be difficult taking HIV medicines every day. We are interested in finding out what it is like for you. Being honest about whether or not you take your medicines may help others in the future. Please tick the answer that best describes what is happening to you. Please only think about the HIV medicines you are taking, and not any other medicines. Thank you for your help*

1. Some people find that they forget to take their medicines at the weekend. Did you miss any of your HIV medicines last weekend (Friday, Saturday or Sunday)?
- Yes ☐  
No ☐

2. When was the last time you missed any HIV medicine doses? (please tick one box)
- Within the last week ☐  
1-2 weeks ago ☐  
3-4 weeks ago ☐  
1-3 months ago ☐  
Not at all since last visit ☐

3. Some people find that they aren't able to take medicines every day. Have you missed all of your HIV medicines for two days or more in a row since your last clinic visit?
- Yes ☐  
No ☐

4. Please mark on the line below the amount of HIV medicine doses you have taken since your last clinic visit.  
e.g. 0% would mean "I haven't taken any of my HIV medicine doses" and 100% would mean "I have taken all of my HIV medicine doses"

[figure not shown]

5. Did you complete this form on your own?
- Yes ☐  
No ☐ If No, who else was involved?  
(e.g parent, nurse, friend)

*Thank you for taking the time to complete this form. Please add any comments that you may have here:*

Carers  
Both Groups  
Screening

[figure not shown]

**ADHERENCE QUESTIONNAIRE FOR CARERS**  
**Both Groups – SCREENING**

|                                                               |                               |                                      |  |
|---------------------------------------------------------------|-------------------------------|--------------------------------------|--|
| Trial number: _____                                           |                               | Date of birth:    /    /             |  |
| Male  Female  | Date of assessment:    /    / | Date of last clinic visit:    /    / |  |

*We know that it can be difficult giving HIV medicines to your child every day. We are interested in finding out what it is like for you and your family. Being honest about whether or not your child takes their medicines may help others in the future. Please tick the answer that best describes what is happening as far as you know. Please only think about the HIV medicines your child is taking, and not any other medicines.*

*If your child is responsible for taking their own medicines then you do not need to complete this questionnaire. Thank you for your help.*

- What is your relationship to the child? \_\_\_\_\_
- Who gives medicines to your child? (eg. you/ your partner/ other family member) \_\_\_\_\_
- Some people find that they forget to take their medicines at the weekend. Did your child miss any of their HIV medicines last weekend (Friday, Saturday or Sunday)? Yes ☐ No ☐
- When was the last time the child missed any HIV medicine doses? (please tick one box)
 

|                             |                          |
|-----------------------------|--------------------------|
| Within the last week        |  |
| 1-2 weeks ago               |  |
| 3-4 weeks ago               |  |
| 1-3 months ago              |  |
| Not at all since last visit |  |
- Some people find that they aren't able to take medicines every day. Has your child missed all their HIV medicines for two days or more in a row since their last clinic visit? Yes ☐ No ☐
- Please mark on the line below the amount of HIV medicine doses your child has taken since their last clinic visit.  
e.g. 0% would mean "They haven't taken any of their HIV medicine doses" and 100% would mean "They have taken all of their HIV medicine doses"

[figure not shown]

- Did you complete this form alone? Yes ☐ NO ☐ If No, who else was involved? (e.g. nurse, doctor) \_\_\_\_\_

Thank you for taking the time to complete this form. Please add any comments that you may have here:

Young People  
Weekends off  
Follow-Up

[figure not shown]

**ADHERENCE QUESTIONNAIRE FOR YOUNG PEOPLE**  
**Weekends off Group – FOLLOW-UP**

|                                                               |                         |                     |                     |
|---------------------------------------------------------------|-------------------------|---------------------|---------------------|
| Trial number: _____                                           |                         | Date of birth: / /  |                     |
| Male  Female  | Date of assessment: / / | Week no: (tick one) | 4 12 24 36 48 other |

We know that it can be difficult taking HIV medicines every day. We are interested in finding out what it is like for you. Being honest about whether or not you take your medicines may help others in the future. Please tick the answer that best describes what is happening to you. Please only think about the HIV medicines you are taking, and not any other medicines. Thank you for your help

1. Which HIV medicine doses are you supposed to miss as part of this trial? (Please tick 4 boxes for a twice daily regimen, and 2 boxes for a once daily regimen)

|          | AM                       | PM                       |
|----------|--------------------------|--------------------------|
| Friday   |  |  |
| Saturday |  |  |
| Sunday   |  |  |

2. Since your last clinic visit did you miss all the doses you were supposed to miss?

Yes ☐ Go to Q4  
No ☐ Go to Q3

3. a. If no, how many weekend breaks did you take?

(write number in box)

- b. Please give reasons for not taking a break: (Tick all that apply)

Told not to miss weekend doses by doctor ☐  
Didn't want to miss weekend doses ☐  
Forgot to miss weekend doses ☐  
Didn't understand about missing weekend doses ☐  
Other ☐

If other, please specify here:

4. Since your last clinic visit, did you always restart your HIV medicine doses immediately after your weekend breaks?

Yes ☐ Go to Q6  
No ☐ Go to Q5

5. If no, after how many weekends did you not restart your doses immediately after the weekend break?

(write number in box)

6. When was the last time you missed any HIV medicines apart from those allowed at the weekend? (please tick one box)

Within the last week ☐  
1-2 weeks ago ☐  
3-4 weeks ago ☐  
1-3 months ago ☐  
Not at all since last visit ☐

7. Please mark on the line below the amount of HIV medicine you have taken since your last clinic visit (please ignore any breaks that are allowed at the weekend).  
e.g. 0% would mean "I haven't taken any of my HIV medicine doses" and 100% would mean "I have taken all of my HIV medicine doses when I was supposed to (i.e. taken the breaks as my doctor told me)"

[figure not shown]

Please turn over

8. Did you complete this form alone?

Yes ☐  
No ☐

If No, who else was involved?  
(e.g parent, nurse, friend)  
\_\_\_\_\_

*Thank you for taking the time to complete this form. Please add any comments that you may have here:*

Carers  
Weekends off  
Follow-Up

[figure not shown]

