### Main Trial

Young people randomised to SCT will follow a cycle of 5 days on ART (Monday-Friday or Sunday-Thursday) and 2 days off (Saturday-Sunday or Friday-Saturday)\*. Participants randomised to the SCT arm and included in this phase of the trial may choose which 2 days off ART they would prefer and whichever are chosen must be continued throughout the entire time on SCT within the study. Young people randomised to continuous ART will continue their current ART regimen\*\*.

\*Young people randomised to SCT can choose to take 2 consecutive days off during the week other than Saturday-Sunday or Friday-Saturday if these are the days that vary from their normal routine (for example, if a young person stays with a different family member on 2 days of the week then those 2 days could be the days taken off ART). The 2 days to be taken off should be decided at enrolment and should be adhered to throughout the study period.

**\*\***Young people randomised to continuous ART should only stop or switch all drugs in their ART regimen for virological, immunological or clinical failure according to local practice. However if simplification of the ART regimen or substitution of one drug is deemed necessary for clinical reasons, this may be allowed after discussion with the appropriate Trials Unit.

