## 7.3 Specific Requirements for the Main Trial

Participants enrolled in the main phase of the trial will be able to choose the days off (Friday-Saturday or Saturday-Sunday)\*. Whichever is chosen must be continued throughout the entire time on SCT within the study.

\*Consecutive days off alternative to Saturday-Sunday or Friday-Saturday can be chosen to better suit a young person's normal routine.

The two days off ART treatment indicated by the participant at screening should be confirmed on the Trial Entry form. It should be made very clear that the chosen 2 days off should remain the same throughout the length of the trial.

Participants in the main phase of the trial should be asked to come to the randomisation visits as soon as possible following the screening visits (once eligibility has been confirmed and within a maximum of 4 weeks), having fasted from the previous evening.

A full clinic visit should be scheduled for 4 weeks after the randomisation visit i.e. a week 4 visit.

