6. Since their last clinic visit, did your child always restart their HIV medicine doses immediately after their weekend breaks?

|     |                          |          |
|-----|--------------------------|----------|
| Yes |  | Go to Q8 |
| No  |  | Go to Q7 |

7. If no, after how many weekends did your child not restart their doses immediately after the weekend break?

(write number in box)

8. When was the last time your child missed any HIV medicines apart from those allowed at the weekend? (please tick one box)

|                             |                          |
|-----------------------------|--------------------------|
| Within the last week        |  |
| 1-2 weeks ago               |  |
| 3-4 weeks ago               |  |
| 1-3 months ago              |  |
| Not at all since last visit |  |

Please turn over

9. Please mark on the line below the amount of HIV medicine doses your child has taken since their last clinic visit (please ignore any breaks that are allowed at the weekend).  
e.g. 0% would mean "They haven't taken any of their HIV medicine doses" and 100% would mean "They have taken all of their HIV medicine doses when they were supposed to (i.e. taken the breaks as directed by the doctor)"

[figure not shown]

10. Did you complete this form alone?

Yes ☐  
No ☐

If No, who else was involved?  
(e.g nurse, doctor)

\_\_\_\_\_

*Thank you for taking the time to complete this form. Please add any comments that you may have here:*

Young people  
Continuous  
Follow-up

[figure not shown]

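### The SCT follow-up adherence forms recognise only Friday-to-Sunday breaks, although the protocol allows other agreed days off, so permitted breaks may be reported as recent missed doses

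*Combined protocol and SAP*

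**What the plan says.** **The day-off rule.** Under Main Trial, Sections 1.2 and 4.1 say that SCT participants "can choose to take 2 consecutive days off during the week other than Saturday-Sunday or Friday-Saturday", on the condition "if these are the days that vary from their normal routine". Section 7.3 repeats the permission: "Consecutive days off alternative to Saturday-Sunday or Friday-Saturday can be chosen to better suit a young person's normal routine". The choice is documented: "The two days off ART treatment indicated by the participant at screening should be confirmed on the Trial Entry form". Pilot participants had Saturday-Sunday off and could later change only to Friday-Saturday (Section 7.1).

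**The forms.** Appendix 4 has SCT follow-up forms for young people and for carers.
- Item 1 asks "Which HIV medicine doses are you supposed to miss as part of this trial" and offers rows for Friday, Saturday and Sunday only. Carer item 3 has the same grid.
- Items 3 to 5 (carer items 5 to 7) ask about breaks and restarting in terms of weekends.
- Item 6 asks "When was the last time you missed any HIV medicines apart from those allowed at the weekend". Carer item 8 asks "When was the last time your child missed any HIV medicines apart from those allowed at the weekend". The most recent answer category is the past week.
- Item 7 (carer item 9) is a 0-100% line with the instruction "please ignore any breaks that are allowed at the weekend".

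**The use made of them.** Adherence from participant-completed questionnaires, over 48 weeks and over the whole trial, is a secondary outcome (Sections 1.4, 4.2 and 11.2).

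**The concern.** The forms appear to have been written for weekend breaks only. A participant whose agreed break falls midweek has no correct answer to item 1, yet Section 8.6 asks for every question to be answered and for site staff to check completeness. Item 6 then exempts only weekend breaks, so an agreed weekday break counts as a miss if the wording is taken at face value.

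The continuous-arm form needs no exemption because that arm has no days off. Any error therefore falls on one side of a between-arm comparison and makes SCT look worse. Items 4 and 5 are also the form's direct question about late restarting, which Sections 2.6 and 8.7 name as a risk of the strategy. Because they ask only about weekends, an extended weekday break could go unrecorded on the form.

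**Working it through.** There is no figure in the plan to reproduce. The check compares the rule with the form items and then illustrates the size.

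**Step 1: which pairs fit the grid.** A week has seven consecutive pairs of days. A Friday-to-Sunday grid fully shows two of them (Friday-Saturday and Saturday-Sunday). Two more are half shown (Thursday-Friday and Sunday-Monday). Three cannot be shown at all (Monday-Tuesday, Tuesday-Wednesday and Wednesday-Thursday).

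**Step 2: item by item, for an agreed weekday break.**

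| Young person (carer) item | Wording | Effect |
|---|---|---|
| 1 (3) | Friday to Sunday only | Cannot be completed correctly |
| 2 (4) | Planned doses to miss, no day named | Works |
| 3-5 (5-7) | Weekend breaks | Poor fit; item 3 is reached only after a no at item 2 |
| 6 (8) | Exempts weekend breaks only | Literal answer: a miss in the past week, at each visit |
| 7 (9) | Instruction names the weekend; the 100% anchor counts breaks taken as the doctor said | Ambiguous |

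**Step 3: size on item 6 (carer item 8).** Let *f* be the share of the SCT arm with weekday breaks and *p* the true proportion with an unplanned miss in the past week. The documents give neither, so both are assumed. If everyone affected answers literally:

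observed rate = *p* + *f*(1 − *p*), so the rise is *f*(1 − *p*).

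| *f* | People out of 80 | Rise at *p* = 5% | Rise at *p* = 10% | Rise at *p* = 20% |
|---|---|---|---|---|
| 5% | 4 | 4.8 points | 4.5 | 4.0 |
| 10% | 8 | 9.5 | 9.0 | 8.0 |
| 20% | 16 | 19.0 | 18.0 | 16.0 |

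For example, with *f* = 10% and *p* = 10%: 0.10 + 0.10 × 0.90 = 19.0% observed against 10% true. The 80 is the minimum per arm in Section 11.3. If everyone affected reads weekend as their own break, the rise is zero.

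**Step 4: size on item 7 (carer item 9), worst case.** A fully adherent person who ignores the printed anchor and counts all seven days would mark 5/7 = 71% instead of 100%. The arm mean then falls by *f* × 2/7, which is 1.4, 2.9 or 5.7 points for *f* = 5%, 10% or 20%. A person who follows the anchor marks 100% and there is no fall.

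**The case against.** Several counter-arguments stand.

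- **Weekend is the trial's own label for the SCT break.** The forms are headed as the weekends-off group, and Section 8.7 and Appendix 15 use the word in the same way. A participant with agreed alternative days may well read it as their own break.
- **The forms are partly neutral about days.** Item 2 and the 100% anchor of item 7 treat the agreed break as adherent, so 71% is a worst case.
- **The permission is conditional, and pilot participants fall outside it.** Alternative days depend on the normal routine. With about 15 pilot SCT participants excluded, an arm of 80 leaves about 65 who could be affected.
- **Adherence is monitored in other ways.** Section 8.7 names viral load first, then questionnaires, diaries and MEMS caps. The diaries in Appendix 7 record doses day by day, so they can show an extended break whichever days were chosen.

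A reader might infer that permitted weekday breaks are coded as missed doses and that SCT adherence is therefore understated. The documents do not support that. They contain no such coding rule, and they do not say how many participants chose other days. Nor do they make these forms the only or main check on extended breaks.

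What survives is narrower. Item 1 has no correct answer for these participants under any reading, and item 6 has no neutral anchor to correct its wording. The other sources do not repair the secondary outcome, because that outcome is defined from the questionnaires.

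**Conclusion.** The day-off rule and the SCT follow-up forms do not match, and this should be put right. Participants with agreed weekday breaks cannot complete item 1 (carer item 3) correctly. A literal answer to item 6 (carer item 8) may record a permitted break as a recent miss, in the SCT arm only. Item 7 (carer item 9) is ambiguous rather than biased in a known direction.

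The possible rise in the SCT recent-miss rate runs from zero to about 19 points. The upper end needs three assumptions that the documents do not settle: 20% of the arm with weekday breaks, every one of them answering literally, and a true recent-miss rate as low as 5%. If few participants chose other days, the effect is small. It concerns a self-reported secondary outcome; the virological primary outcome is not touched.

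**What to change.** **Forms still in use.** In both SCT follow-up forms (young person and carer), extend the grid to all seven days and replace the weekend wording with *your agreed two days off*. This still has value because Sections 1.13 and 8.10 continue the adherence questionnaire every 12-16 weeks in long-term follow-up. It comes too late for forms up to week 48: the current protocol is dated May 2015, and the amendment log puts the end of recruitment at June 2013.

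**Forms already completed.**
1. Identify participants with weekday breaks from the Trial Entry form.
2. Flag their answers to items 1 and 3-7 (carer items 3 and 5-9).
3. Interpret item 6 (carer item 8) against the diary where one is available. The Trial Entry days alone cannot recode it, because they do not show whether a reported miss was the agreed break or a true one.
4. Keep these participants in the main comparison, report how many there are, and add a sensitivity analysis without the flagged answers.

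**Cost.** Revised wording, its translation, and one flag derived from data already collected. There are two downsides. Form versions will differ slightly over time, and the sensitivity analysis removes people from one randomised arm only, so it should not replace the main comparison.
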